# Thromboelastometry versus standard coagulation tests versus restrictive protocol to guide blood transfusion prior to central venous catheterization in cirrhosis: study protocol for a randomized controlled trial

**DOI:** 10.1186/s13063-017-1835-5

**Published:** 2017-02-27

**Keywords:** Blood coagulation tests, Blood transfusion, Catheterization, Central venous, Clinical trial, Critical care, Hemostatic disorders, Liver failure, Thromboelastography, Ultrasonography, Vascular access devices

## Abstract

**Background:**

Liver failure patients have traditionally been empirically transfused prior to invasive procedures. Blood transfusion is associated with immunologic and nonimmunologic reactions, increased risk of adverse outcomes and high costs. Scientific evidence supporting empirical transfusion is lacking, and the best approach for blood transfusion prior to invasive procedures in cirrhotic patients has not been established so far.

The aim of this study is to compare three transfusion strategies (routine coagulation test-guided – ordinary or restrictive, or thromboelastometry-guided) prior to central venous catheterization in critically ill patients with cirrhosis.

**Methods/design:**

Design and setting: a double-blinded, parallel-group, single-center, randomized controlled clinical trial in a tertiary private hospital in São Paulo, Brazil. Inclusion criteria: adults (aged 18 years or older) admitted to the intensive care unit with cirrhosis and an indication for central venous line insertion. Patients will be randomly assigned to three groups for blood transfusion strategy prior to central venous catheterization: standard coagulation tests-based, thromboelastometry-based, or restrictive. The primary efficacy endpoint will be the proportion of patients transfused with any blood product prior to central venous catheterization. The primary safety endpoint will be the incidence of major bleeding. Secondary endpoints will be the proportion of transfusion of fresh frozen plasma, platelets and cryoprecipitate; infused volume of blood products; hemoglobin and hematocrit before and after the procedure; intensive care unit and hospital length of stay; 28-day and hospital mortality; incidence of minor bleeding; transfusion-related adverse reactions; and cost analysis.

**Discussion:**

This study will evaluate three strategies to guide blood transfusion prior to central venous line placement in severely ill patients with cirrhosis. We hypothesized that thromboelastometry-based and/or restrictive protocols are safe and would significantly reduce transfusion of blood products in this population, leading to a reduction in costs and transfusion-related adverse reactions. In this manner, this trial will add evidence in favor of reducing empirical transfusion in severely ill patients with coagulopathy.

**Trial registration:**

ClinicalTrials.gov, identifier: NCT02311985. Retrospectively registered on 3 December 2014.

**Electronic supplementary material:**

The online version of this article (doi:10.1186/s13063-017-1835-5) contains supplementary material, which is available to authorized users.

## Background

Central venous catheterization (CVC) is a routine procedure in the intensive care unit (ICU) [1]. In the USA alone, more than 15 million catheter-days are reported annually [2]. Bleeding is the most common complication of CVC [3], with an incidence of between 12 per 1000 [4] and 94 per 1000 catheter insertions [5], and may be life-threatening in severe cases. More recently, the use of ultrasound guidance for CVC has significantly decreased overall mechanical complication rates [6–10] and is safe in patients with coagulopathy [11].

Patients with liver failure are classically believed to be prone to bleeding disorders [12]. Currently, approximately 9 out of 10 ICU physicians empirically transfuse liver failure patients before invasive procedures [13]. However, scientific evidence for this practice is lacking. Recent medical literature evidence now shows that patients with liver failure exhibit a rebalancing ability between anticoagulant and procoagulant factors [12] and have thrombin generation comparable to healthy individuals [14]. Thus, bleeding in those patients may be mainly related to circulatory and endothelial alterations instead of coagulation disorder per se. In spite of that, several physicians rely on standard coagulation tests (SCTs), i.e., prothrombin time (PT), international normalized ratio (INR), activated partial thromboplastin time (aPTT) and platelet count, to guide blood transfusion before CVC in patients with cirrhosis [15, 16].

It has been shown that SCTs reflect a limited view of coagulation status (isolated plasmatic component evaluation) [17, 18] and do not accurately predict bleeding risk in patients with suspected coagulopathy [18–21]. Specifically, patients with liver disease and prolonged PT/aPTT may have coagulation factor levels above the sufficient for adequate clot formation [22]. Moreover, attempts to correct (or normalize) standard coagulation tests by transfusion do not guarantee coagulopathy reversal [23, 24] and to insist on this practice may increase the risk of transfusion-related complications, including death [25].

Rotational thromboelastometry (ROTEM®) is a point-of-care test that evaluates coagulation according to the viscoelastic properties of a whole blood sample [26]. ROTEM® has the advantage of a more comprehensive (clot initiation, formation and stabilization) and faster (online) bedside coagulation evaluation when compared to SCTs [27]. Clinical protocols based on thromboelastometry have been effective in reducing blood transfusion, costs and mortality in diverse clinical settings [28–31] including liver transplantation [32, 33].

General clinical practice guidelines recommend prophylactic transfusion of blood products prior to invasive procedures based on SCTs alterations [34–36]. Nevertheless, there is no consensus as to whether and how blood transfusion should be used before invasive procedures, particularly in patients with cirrhosis. The majority of available data have originated from small clinical trials and observational studies, which limit an evidence-based approach. The culture of blood transfusion is moving towards a rational evidence-based use of blood and its components [37].

This study will compare three blood transfusion protocols (coagulogram-based, thromboelastometry-based and restrictive) prior to CVC in critically ill patients with cirrhosis. We hypothesized that restrictive and/or thromboelastometry-guided transfusion protocols are safe and would decrease the need of blood products transfusion compared to an ordinary coagulogram-based protocol in critically ill patients with cirrhosis submitted to a CVC.

## Methods/design

### Study design

This is a double-blinded, parallel-group, superiority, single-center, randomized controlled clinical trial.

### Study setting

The participating hospital is a private tertiary 657-bed hospital in São Paulo, Brazil, with an active liver transplant program (mean ± standard deviation (SD) 118 ± 15 liver transplants per year). Patients will be screened and recruited in two mixed medical-surgical intensive care units, with 48 beds in total, and 3673 admissions per year.

### Participants

All adult patients (aged 18 years or older) admitted to the ICU with chronic liver failure and an indication for bedside central venous line placement for intravenous (I.V.) medication administration (including vasopressors), hemodialysis and/or hemodynamic monitoring will be eligible for inclusion. Chronic liver failure will be defined as liver cirrhosis of any etiology diagnosed via biopsy or clinical evaluation. The exclusion criteria will be: acute liver failure, an indication for a peripherally inserted central venous catheter, current use of orally administered (e.g., inhibitors of factor Xa, thrombin and vitamin K-dependent factors) or parenterally administered anticoagulants (e.g., nonfractionated heparin or low-molecular-weight heparin) in full therapeutic dosage, von Willebrand disease and enrollment in another clinical trial with blood transfusion as intervention.

### Laboratory procedures

Before a CVC, every included patient will be submitted to blood sampling for SCTs (PT, INR, aPTT and platelet count), ROTEM® analysis, serum fibrinogen, hemoglobin, hematocrit, ionized calcium and arterial pH. Blood samples of 5 mL will be obtained directly from a peripheral vein by applying a light tourniquet to avoid blood stasis, or from a central venous line after discarding the first 5 mL of blood (in the case of an indication for a second CVC, e.g., hemodialysis catheter), or from an arterial line. Blood samples for SCTs, ROTEM® and fibrinogen will be conditioned in citrate tubes (3.2%; Sarstedt Monovette®, Wedel, Germany) and processed immediately. Blood samples for hemoglobin level, hematocrit and platelet count will be conditioned in 2.6-mL tubes containing EDTA KE (Sarstedt Monovette®, Wedel, Germany).

Thromboelastometry analysis (ROTEM® delta, Pentapharm Co., Munich, Germany) will be performed by pipetting 300 μL citrated whole blood and 20 μL 0.2-M calcium chloride (CaCl_2_) with specific activators into a plastic cup [38]. Extrinsically activated (EXTEM), intrinsically activated (INTEM), and fibrinogen polymerization (FIBTEM) assays will be performed. ROTEM® analysis will run for up to 60 min. The parameters coagulation time (CT; s), clot formation time (CFT; s), maximum clot firmness (MCF; mm), alpha angle (α; degrees) and amplitude at 10 min (A10; mm) will be recorded [38].

The EXTEM assay contains a preparation of human recombinant tissue factor, which activates the coagulation cascade and can assess coagulation status via CT_EXTEM_, CFT_EXTEM_ and MCF_EXTEM_ [27]. The FIBTEM assay uses cytochalasin D which is a potent platelet inhibitor and serves to evaluate fibrinogen function and fibrin polymerization [27]. The A10 is a surrogate marker of MCF and can predict coagulopathy with high sensitivity and specificity (1.0 and 0.7, respectively) with the advantage of a faster evaluation of coagulation disorders [39].

Prothrombin time, INR and aPTT (ACL TOP 700 system, Instrumentation Laboratory, Bedford, MA, USA), serum fibrinogen (Clauss method) and platelet count (Sysmex® XN-Series, Sysmex Corporation, Lincolnshire, IL, USA) will be performed according to the hospital’s standard analytical methods.

### Central venous catheterization

All CVCs will be performed with real-time ultrasound (Bard Site ~ Rite® 5 Ultrasound System, Bard Access Systems, Salt Lake City, UT, USA) guidance, using the modified Seldinger (over the guidewire) technique. Only ICU physicians and medical residents trained in ultrasound-guided vascular access will be allowed to perform the procedures. To obtain a valid training status, the ICU physician must have performed at least 50 ultrasound-guided CVCs and at least 12 ultrasound-guided insertions the previous year. The choice of insertion site (jugular, femoral or subclavian) will be at the inserter’s discretion. All procedures will be performed according to best practices guidelines [40] and audited by a staff nurse. A chest X-ray will be ordered after each procedure (except for femoral vein site) to assess catheter positioning and complications. A blinded-to-intervention nurse will inspect the insertion site for local complications within the first 24 h after catheter placement using the HEME tool checklist [41].

Inclusion in the trial does not preclude concomitant care. The researchers will monitor whether patients will receive any blood transfusion related to the procedure within the first 24 h.

### Interventions

Patients will be randomly assigned to three groups, each including a protocol to guide blood product transfusion (fresh frozen plasma (FFP), platelets and/or cryoprecipitate) prior to CVC, namely: (1) a transfusion protocol based on standard coagulation tests – Coagulogram-based group, (2) a transfusion protocol based on rotational thromboelastometry – Thromboelastometry-based group or (3) a restrictive transfusion protocol – Restrictive group – also based on SCTs, but with wider transfusion trigger values.

### Coagulogram-based group

The Coagulogram-based group (control group) is based on our institutional protocol and takes into account the SCTs PT/INR, aPTT, platelet count and serum fibrinogen levels to guide transfusion prior to CVC (Fig. 1).

**Fig. 1 Fig1:**
[figure not shown]
Coagulogram-based blood transfusion protocol. *INR* international normalized ratio; *aPTT* activated thromboplastin time; *FFP* fresh frozen plasma

Accordingly, if INR ≤1.5, aPTT ≤50 s, platelet count ≥50,000/μL and serum fibrinogen ≥150 mg/dL, no transfusion is indicated. Otherwise, if INR >1.5 or aPTT >50 s, FFP is transfused at 10 mL per kg of body weight; and/or if platelet count <50,000/μL, 1 unit per 10 kg of body weight of random platelets (up to 10 units) or 1 unit of apheresis platelets is transfused; and/or if serum fibrinogen <150 mg/dL, 1 unit per 10 kg of body weight of cryoprecipitate is transfused (up to 10 units).

### Thromboelastometry-based group

The thromboelastometry-based transfusion protocol uses EXTEM and FIBTEM assays from the ROTEM® and was adapted from Görlinger et al. [42] (Fig. 2). No transfusion is necessary when CT_EXTEM_ is ≤80 s and A10_EXTEM_ is ≥40 mm. The CT_EXTEM_ will be used to assess coagulation factor deficiency. For patients in whom CT_EXTEM_ is >80 s, transfusion of 10 mL per kg of body weight of FFP is performed. If the patient presents an A10_EXTEM_ <40 mm, we further evaluate the A10_FIBTEM_. If A10_FIBTEM_ is ≥10 mm (indicating adequate fibrinogen function), random platelet units (1 unit per 10 kg of body weight; maximum 10 units) or 1 unit of apheresis platelets is transfused. Otherwise, if A10_FIBTEM_ is <10 mm (indicating fibrinogen deficiency), cryoprecipitate (1 unit per 10 kg of body weight; maximum 10 units) is transfused.

**Fig. 2 Fig2:**
[figure not shown]
Thromboelastometry-based blood transfusion protocol. *CT* clotting time; *MCF* maximum clot firmness; *A10* amplitude at 10 min; *FFP* fresh frozen plasma

### Restrictive group

The restrictive transfusion protocol is also based on SCTs, but it uses wider transfusion triggers and it does not take into account serum fibrinogen and aPTT levels (Fig. 3). If INR is ≤5.0 and platelet count is ≥25,000/μL, no transfusion is required. If INR is >5.0, FFP is transfused at 10 mL per kg of body weight; and/or platelet count is <25,000/μL, random platelet units (1 unit per 10 kg of body weight; maximum 10 units) or 1 unit of apheresis platelets is transfused.

**Fig. 3 Fig3:**
[figure not shown]
Restrictive blood transfusion protocol. *INR* international normalized ratio; *FFP* fresh frozen plasma

### Study endpoints

The primary efficacy endpoint is the proportion of patients transfused with any blood product (i.e., FFP, platelets or cryoprecipitate) prior to CVC. The primary safety endpoint is the incidence of major bleeding within the first 24 h after catheter insertion. Major bleeding was defined according to the HEME tool [41]. According to the HEME tool, major bleeding is defined as overt bleeding with any of the following (in the absence of other causes): decrease in hemoglobin of 20 g/L or more, transfusion of 2 or more units of RBC with no increase in hemoglobin level, decrease in systolic BP by 10 mmHg or more while the patient is sitting up, spontaneous decrease in systolic BP of 20 mmHg or more or increase in heart rate by 20 bpm or more; bleeding at any one of the following sites: intracranial, intraspinal, intraocular, pericardial, retroperitoneal or intraarticular; or wound-related bleeding requiring an intervention.

The secondary efficacy endpoints will be: the proportion of patients transfused with each blood component and the infused volume of each blood component, hemoglobin and hematocrit levels before and up to 24 h after CVC, costs associated to blood product transfusion and laboratory tests, ICU and hospital length of stay, and ICU, 28-day and hospital mortality. Secondary safety endpoints will include: the incidence of minor bleeding complications (i.e., oozing or hematoma with no criteria for major bleeding) and the proportion of patients transfused due to bleeding within the first 24 h after CVC, and the incidence of acute transfusion-related adverse events (i.e., transfusion-associated cardiac overload, acute hemolytic transfusion reactions, anaphylactic reactions, febrile nonhemolytic reactions and urticarial reactions). The transfusion of bleeding patients after CVC will follow the Hospital Israelita Albert Einstein institutional transfusion protocol. Accordingly, if INR >1.5 or aPTT >32 s, FFP (10 mL per kg) is administered. If serum fibrinogen <150 mg/dL, cryoprecipitate (1 unit per 10 kg) or fibrinogen concentrate (2 to 4 g) is administered. If the platelet count <50 x 10^3^/mm^3^, random platelets (1 unit per 10 kg) or apheresis platelets (1 unit) are administered. Correction of hypothermia (axillary temperature ≥35 °C), hypocalcemia (ionized calcium ≥1.14 mmol/l) and acidosis (pH ≥7.31) is always recommended.

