## Discussion

Our trial is designed to compare three protocols to guide transfusion of blood components prior to CVC in critically ill patients with chronic liver failure. We hypothesized that restricted and thromboelastometry-guided transfusion protocols would be safe and significantly reduce empirical transfusion of blood products in cirrhotic critically ill patients. By reducing transfusion rates, these strategies would also reduce transfusion-related complications and costs. This would help to provide quality evidence for reduction of empirical transfusion of critically ill patients with coagulopathy in clinical practice.

One main focus of our trial is that the transfusion protocols used are based on a comprehensive assessment of coagulation, which includes the contribution of coagulation factors, platelets and fibrinogen. Most randomized trials published so far have relied on a specific aspect of coagulation and a specific blood product transfusion (e.g., FFP transfusion according to PT/INR) [48, 49]. Furthermore, fibrinogen is one of the most important coagulation factors [50], and we believe that including the evaluation of hypofibrinogenemia or dysfibrinogenemia would result in a more detailed understanding of coagulation status and, therefore, help in further prevention of bleeding. Additionally, we will use wide inclusion criteria, accounting for emergency insertions, active bleeding and use of antiplatelet aggregation agents making the case-mix of patients more similar to critical care practice.

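### The closed list that defines the acute transfusion-reaction endpoint omits transfusion-related acute lung injury, so such a case would be left out of this endpoint or counted under the wrong label.

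*Protocol article*

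**What the plan says.** The Study endpoints section names a secondary safety endpoint and defines it by five reactions after *i.e.*: the incidence of "acute transfusion-related adverse events (i.e., transfusion-associated cardiac overload, acute hemolytic transfusion reactions, anaphylactic reactions, febrile nonhemolytic reactions and urticarial reactions"). Transfusion-related acute lung injury appears neither there nor elsewhere in the article.

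The randomized strategies are, in the Interventions section, each "a protocol to guide blood product transfusion (fresh frozen plasma (FFP), platelets and/or cryoprecipitate) prior to CVC". The Discussion paragraph of the abstract includes in the hypothesis that the new strategies would reduce transfusion, "leading to a reduction in costs and transfusion-related adverse reactions". The main Discussion repeats that "these strategies would also reduce transfusion-related complications and costs".

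Other parts of the article also bear on how a serious reaction would be recorded:

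- Data collection, monitoring and interim analysis: every serious adverse event is reported at once to the Ethics Committee and the DSMB. The collected data include adverse events related to the procedure and to transfusion, with no restriction to particular types.
- Randomization, allocation and blinding: the attending physician may be unblinded after a serious transfusion reaction.
- Discussion (limitations): the trial is said to lack adequate power for transfusion complications, whose frequency is put at one in hundreds to thousands of transfusions.

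**The concern.** An endpoint defined by a closed list counts only what is on the list. A non-cardiac lung reaction to a transfusion is none of the five listed entities. An assessor who follows the definition must leave it out or file it under the listed reaction that it most resembles, circulatory overload. Mild events such as urticaria would count, while a potentially severe one would not.

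This matters here because the randomized strategies change how many patients receive plasma and platelets, and fewer transfusion reactions is one of the stated expected benefits. The definition should cover the serious reactions that those products can cause. That lung injury is one of them is general clinical knowledge; the article does not say so. What is at stake is the completeness of one safety tabulation and the comparison drawn from it.

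**Working it through.** **1. Is the list closed?** Compare how the article uses the two abbreviations.

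- *i.e.* before a complete definition, in the same section: the primary efficacy endpoint is transfusion of "any blood product (i.e., FFP, platelets or cryoprecipitate"). Minor bleeding is defined in the same way.
- *e.g.* before open examples, under Participants: "parenterally administered anticoagulants (e.g., nonfractionated heparin or low-molecular-weight heparin").

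The article keeps the two apart, so the natural reading of the five reactions is a full definition.

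**2. Where would a lung-injury case go?**

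- Secondary endpoint, read strictly: not counted.
- Secondary endpoint, if labelled circulatory overload: counted in the overall incidence, but wrong in the breakdown by type.
- Serious adverse event report: sent to the Ethics Committee and the DSMB whatever the endpoint list says.
- General adverse event field: collected, since that field is not limited to the five types.

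The gap is in the endpoint definition, not in the collection of events.

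**3. Does a change touch the sample size?** The trial is sized on the primary efficacy endpoint (Sample size calculation: 90% versus 65%, power 0.80, alpha 0.05). For two proportions with pooled variance and no continuity correction, the mean proportion is 0.775 and

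n = [1.960 × √(2 × 0.775 × 0.225) + 0.842 × √(0.90 × 0.10 + 0.65 × 0.35)]² / 0.25²

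= [1.960 × 0.5906 + 0.842 × 0.5635]² / 0.0625 = 42.6, rounded up to 43.

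This reproduces the plan's 43 per group. Adding its 8 and 4 gives 55 per group, and 3 × 55 = 165. None of these figures depends on the list of reactions.

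**4. How many events could be omitted?** Patients transfused before catheterization at the planned rates:

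- Coagulogram-based group: 55 × 0.90 = 49.5
- Thromboelastometry-based and Restrictive groups: 55 × 0.65 = 35.75 each
- Total: 49.5 + 2 × 35.75 = 121

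The article gives no rate for lung injury, so a risk r per transfused patient is **assumed**, from 1/100 to 1/5000. The range is guided by the order of magnitude in the Discussion, which counts all complications together and per transfusion rather than per patient. Expected omitted events are 121 × r, and the chance of at least one is 1 − (1 − r)^121.

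| Assumed r | Control group | Each new-strategy group | All groups | Chance of at least one |
|---|---|---|---|---|
| 1/100 | 0.50 | 0.36 | 1.21 | 70% |
| 1/500 | 0.10 | 0.07 | 0.24 | 22% |
| 1/1000 | 0.05 | 0.04 | 0.12 | 11% |
| 1/5000 | 0.01 | 0.01 | 0.02 | 2% |

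Even at 1/100, the expected difference between the control group and one new-strategy group is 0.495 − 0.3575 = 0.14 events.

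**The case against.** The best case for leaving the text alone has four parts.

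- **A serious case is seen anyway.** This stands. A reader might infer from the closed list that a severe lung reaction would go unnoticed or be hidden from the DSMB. The article does not support that: serious adverse events are reported at once, transfusion-related adverse events are collected without limit of type, and a serious transfusion reaction can lead to unblinding.
- **A case labelled as overload still counts.** This also stands for the overall incidence. Only the breakdown by type would then be wrong. The article gives no coding rules, so which way a case would go cannot be settled from the text.
- **The article is condensed, and the full protocol may define reactions more broadly.** The abstract lists transfusion-related adverse reactions without restriction. But this is not an item left for another document: the article gives the definition, and gives it as complete. The words that introduce the safety endpoints are open, but they govern which endpoints are listed, not what this one contains.
- **The events are too rare to matter.** The article concedes low power for transfusion complications, and the figures above agree. That explains why no difference may be shown. It is no reason to leave a serious category out of the definition.

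The clinical premise comes from outside the article. It is general knowledge rather than a remembered figure from a source, and no numerical result here depends on it except through the assumed range.

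**Conclusion.** The point holds, as a minor one. As written, the endpoint would exclude or mislabel a transfusion-related lung injury while counting urticaria and fever, in a trial whose arms differ in plasma and platelet exposure and whose authors expect fewer reactions. The loss is limited to this endpoint's tabulation and between-group comparison. Oversight of serious events, sample size and power are untouched.

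The size is about 1.2 to 0.02 omitted events in the whole trial. This rests on the planned transfusion rates, on 55 patients per group, and on an assumed risk of 1/100 to 1/5000 per transfused patient. Patients transfused only after the procedure are not in the 121. It would be wrong to conclude that a real difference between the groups would be lost: with well under one expected event per group, no test could show one with or without the change. The gain is a more complete safety report.

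**What to change.** In the Study endpoints section, add transfusion-related acute lung injury to the five reactions and end the list with any other acute transfusion reaction. Make the same change on the case report form. Classify cases from the adverse event and serious adverse event records that the trial already collects.

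Do not rely on the post-procedure chest X-ray for this. Under Central venous catheterization, it is ordered to check catheter position and complications, and it is not done for femoral lines.

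The cost is one line in the protocol and one on the case report form. Because recruitment is under way, the change is an amendment that needs Ethics Committee approval. The limitation is that some cases may remain hard to tell apart from circulatory overload. The closing category keeps them in the overall incidence even where the type stays uncertain.
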